# Effect of etelcalcetide on cardiac hypertrophy in hemodialysis patients: a randomized controlled trial (ETECAR-HD)

**DOI:** 10.1186/s13063-019-3707-7

**Published:** 2019-10-24

**Keywords:** Hemodialysis, Left ventricular hypertrophy, Secondary hyperparathyroidism, FGF23, Etelcalcetide, Alfacalcidol

## Abstract

**Background:**

Fibroblast growth factor 23 (FGF23) is associated with left ventricular hypertrophy (LVH) in patients with chronic kidney disease, and calcimimetic therapy reduces plasma concentrations of FGF23. It remains unknown whether treatment with the calcimimetic etelcalcetide (ETL) reduces LVH in patients on hemodialysis.

**Methods/design:**

This single-blinded randomized trial of 12 months duration will test the effects of ETL compared with alfacalcidol on LVH and cardiac fibrosis in maintenance hemodialysis patients with secondary hyperparathyroidism. Both treatment regimens will be titrated to equally suppress secondary hyperparathyroidism while alfacalcidol treatment causes an increase and ETL a decrease in FGF23, respectively.

Patients treated thrice weekly with hemodialysis for ≥ 3 months and ≤ 3 years with parathyroid hormone levels ≥ 300 pg/ml and LVH will be enrolled in the study.

The primary study endpoint is change from baseline to 12 months in left ventricular mass index (LVMI; g/m^2^) measured by cardiac magnetic resonance imaging. Sample size calculations showed that 62 randomized patients will be necessary to detect a difference in LVMI of at least 20 g/m^2^ between the two groups at 12 months. Due to the strong association of volume overload and LVH, randomization will be stratified by residual kidney function, and regular body composition monitoring will be performed to control the volume status of patients.

Study medication will be administered intravenously by the dialysis nurses after every hemodialysis session, thus omitting adherence issues.

Secondary study endpoints are cardiac parameters measured by echocardiography, biomarker concentrations of bone metabolism (FGF23, vitamin D, parathyroid hormone, calcium, phosphate, s-Klotho), cardiac markers (pro-brain natriuretic peptide, pre- and postdialysis troponin T) and metabolites of the renin–angiotensin–aldosterone cascade (angiotensin I (Ang I), Ang II, Ang-(1–7), Ang-(1–5), Ang-(1–9), and aldosterone).

**Discussion:**

The causal inference and pathophysiology of LVH regression by FGF23 reduction using calcimimetic treatment has not yet been shown. This intervention study has the potential to discover a new strategy for the treatment of cardiac hypertrophy and fibrosis in patients on maintenance hemodialysis. It might be speculated that successful treatment of cardiac morphology will also reduce the risk of cardiac death in this population.

**Trial registration:**

European Clinical Trials Database, EudraCT number 2017-000222-35; ClinicalTrials.gov, NCT03182699. Registered on

## Background

Patients with chronic kidney disease (CKD) develop left ventricular hypertrophy (LVH) and cardiac fibrosis which contributes to congestive heart failure, diastolic dysfunction, arrhythmia and sudden death [1–3]. The majority of patients with terminal renal failure treated by dialysis exhibit LVH and have a dramatically increased risk of sudden cardiac death [4].

The main drivers of cardiac remodeling in hemodialysis patients are chronic volume overload, intradialytic weight gain and hemodynamic fluctuations during hemodialysis treatment [5, 6]. Additional factors include elevated fibroblast growth factor 23 (FGF23) levels in CKD and dialysis patients and angiotensin II (Ang II)-mediated cardiac remodeling [7, 8]. Circulating concentrations of FGF23 increase progressively as the glomerular filtration rate declines, beginning as early as CKD stage 3b [9–14]. The biological effects of FGF23 are mediated through a receptor complex consisting of FGF receptors (FGFRs) and of the co-receptor α-Klotho, which enables proper FGF23 signaling in target tissues such as the kidney [15].

The left ventricular mass index (LVMI) rises with increasing FGF23 as does the prevalence of eccentric and concentric hypertrophy [2]. The pathophysiological mechanism by which FGF23 may cause LVH is still not well understood and two potentially synergistic hypotheses are discussed in the scientific community.

Wolf et al. showed a direct effect of FGF23 on myocardial hypertrophy. FGF23 treatment of isolated neonatal mouse cardiomyocytes caused an increase in surface area and an activation of pro-hypertrophic gene programs that was independent of Klotho and mediated through FGFR4 [1, 2, 16].

Andrukhova et al. proposed a complementary concept by stating that FGF23-induced Na^+^ and Ca^2+^ retention, volume overload and hypertension are the most determinant factors underlying the pro-hypertrophic effects [17–19]. The investigators were able to show that a low-dose anti-FGF23 antibody treatment substantially ameliorated disease progression and left ventricular dysfunction by preventing the abovementioned volume overload and its consequences on the circulation (unpublished data). Additionally, they showed that the administration of chlorothiazide completely prevents FGF23-induced volume expansion and heart hypertrophy [17].

Recently, Slavic et al. provided evidence of increasing levels of FGF23 and Klotho in a mouse model with pressure overload-induced LVH. They identified aldosterone to be an important stimulator of bone FGF23 transcription following pressure overload [20].

The association of FGF23 and LVH via an activation of the renin–angiotensin–aldosterone system (RAAS) through suppression of angiotensin-converting enzyme 2 (ACE2), and therefore increasing its product Ang-(1–7), have been described previously [21–29]. An overactive RAAS has been linked to multiple pathological processes such as LVH and heart failure, and medications inhibiting the RAAS are capable of improving both [7, 8, 30–32].

The HEMO study investigated a cohort of 1340 hemodialysis patients and found that higher FGF23 levels were a predictor of cardiac events, infections and all-cause mortality [33]. Various studies, such as PARADIGM, demonstrated that the oral calcimimetic drug cinacalcet causes a reduction in the level of FGF23 of at least 30%, while the intake of vitamin D analogs causes an increase of over 40%. Both treatments cause similar modest reductions in parathyroid hormone (PTH) levels [34–37].

In this trial, the level of FGF23 will be modified by either the calcimimetic etelcalcetide (ETL) or alfacalcidol (ALFA) at a PTH clamp, and therefore will be able to test the causality of FGF23 reduction on cardiac hypertrophy and fibrosis.

## Methods/design

### Study design

In this randomized, controlled, single-blinded trial, we will study the effect of the calcimimetic drug ETL in comparison with the active vitamin D ALFA on LVH and cardiac fibrosis in hemodialysis patients with secondary hyperparathyroidism (sHPT).

The treatment will be administered intravenously by dialysis nurses in addition to conventional HPT therapy (phosphate binders, calcium supplementation) in 62 subjects for 12 months. LVH will be measured as LVMI by cardiac magnetic resonance imaging (cMRI). The inclusion and exclusion criteria for participants are listed in Table 1. Patients will be recruited from two hemodialysis centers of the Medical University of 144 Vienna with 160 prevalent patients and the Vienna Dialysis Center with 300 prevalent 145 patients. The present protocol follows the Standard Protocol Items: Recommendations for Interventional Trials (SPIRIT) guidelines and fulfills the SPIRIT checklist (see Additional file 1).

**Table 1 Tab1:** Main inclusion and exclusion criteria

Main inclusion criteria	
Age ≥ 18 years	
Maintenance hemodialysis 3×/week for ≥ 3 months and ≤ 3 years	
sHPT defined by:	
• PTH ≥ 300 pg/mL and no prior calcimimetic drug, or	
• PTH ≥ 300 pg/mL after washout of vitamin D for 4 weeks	
• Patients after washout of cinacalcet for 4 weeks	
Serum calcium ≥ 2.08 mmol/L	
LVH ± cardiac fibrosis on echocardiography	
Optimal fluid composition (BCM measurement); pulmonary edema excluded (lung ultrasound)	
No substantial dose change of calcium supplements, phosphate binders, dialysate calcium, or active vitamin D for 4 weeks before screening	
Main exclusion criteria	
Unstable medical condition	
Significantly impaired LV systolic function or hemodynamically effective heart valve defects	
Anticipated parathyroidectomy	
Scheduled kidney transplant from a living donor	
Uncontrolled hyperphosphatemia	
Active participation in another clinical trial	
Sensitivity or intolerance to administered products	
Women who are pregnant or breast feeding	
Disorder compromising the ability to give informed consent and/or to comply with the study procedures	
Contraindications for MRI	

*BCM* body composition monitoring, *LV* left ventricular, *LVH* left ventricular hypertrophy, *MRI* magnetic resonance imaging, *PTH* parathyroid hormone, *sHPT* secondary hyperparathyroidism

### Screening, washout phase and randomization

The study flow chart and design are presented in Figs. 1 and 2, respectively. Following signed informed consent, patients will be screened for LVH (i.e., interventricular septum thickness ≥ 12 mm) and cardiac fibrosis using strain echocardiography. Volume status and fluid composition will be explored with the help of body composition monitoring (BCM) and lung ultrasound [38–41]. Only patients who are stable at their dry weight are eligible for enrollment to the study. All patients that are already being treated with a calcimimetic drug or vitamin D therapy will undergo a 4-week-long washout phase in which the treatment will be discontinued. Study participants who qualify for the study will be randomized at a 1:1 ratio to the ETL group or the ALFA group. Randomization will be performed by a computer algorithm (www.meduniwien.ac.at/randomizer/web) and will be stratified by residual kidney function (< 500 ml versus ≥ 500 ml urine per day) and the center where patients are recruited (Medical University of Vienna versus Vienna Dialysis Center). To ensure that comparison groups will be of approximately the same size and balanced in each center, a block randomization (block size of 4) will be used.

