### Outcome measurements

#### Cardiac MRI

Two cMRIs are planned for each patient. The baseline MRI will take place before randomization and the second MRI will take place after completing 12 months of treatment. Both will be carried on the dialysis-free day.

The cMRI will be analyzed by one radiologist blinded to the treatment allocation. Noncontrast cMRI will be carried out using a 1.5-Tesla MRI scanner (Siemens Avanto 1.5 T, Siemens, Erlangen, Germany). Axial black-blood imaging will be performed for visualization of cardiac anatomy. For the assessment of cardiac function, left ventricular muscle mass, and the visualization of possible wall motion abnormalities, multislice-multiphase cine imaging will be performed in the long horizontal axis as well as in the short axis view through the entire heart. The ejection fraction (in percent) of both the left and right ventricles will be calculated in a semiautomatic fashion using dedicated software (Siemens Argus) based on the short axis views. For the assessment of cardiac function, the end-diastolic and end-systolic volume (in milliliters) will be assessed in a semiautomatic fashion and the left ventricular muscle mass will be calculated [42]. The upper limit of normal left ventricular mass indexed for body surface area (LVM/BSA) values is considered to be 84.1 g/m^2^ for male and 76.4 g/m^2^ for female subjects [6].

For the detection of myocardial fibrosis, fat-suppressed T2-weighted edema-sensitive imaging will be performed. Noncontrast T1 mapping will be performed to detect diffuse fibrotic processes (T1 time is measured in milliseconds for global, septal and nonseptal times). The native myocardial T1 relaxation is a surrogate of myocardial fibrosis [43]. In hemodialysis patients the interventricular septum appears to be particularly prone to the development of fibrosis [44].

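### A single constant block size of 4, in a trial whose investigators very likely know the assigned drug, could make about 31% of allocations deducible in advance

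*Protocol article*

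**What the plan says.** The protocol article's section on screening, washout and randomization says that qualifying patients "will be randomized at a 1:1 ratio to the ETL group or the ALFA group". "Randomization will be performed by a computer algorithm", which "will be stratified by residual kidney function" (below 500 ml of urine per day, or 500 ml and above) and by centre, of which there are two. The blocks have a stated purpose, "To ensure that comparison groups will be of approximately the same size and balanced in each center", and one stated size: "a block randomization (block size of 4) will be used". The article does not mention varying the size or keeping it from recruiting staff.

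On blinding, Study design opens with "In this randomized, controlled, single-blinded trial". The staff described as blinded are outcome assessors: the cardiac MRI is "analyzed by one radiologist blinded to the treatment allocation", and the echocardiography section blinds the examining physician. Under Investigational products, each drug has its own dose units, titration steps and laboratory limits. Under Other HPT treatments, a rescue rule applies to one arm only and is left to the investigator's decision.

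**The concern.** Permuted blocks keep the arms balanced by forcing each block to even out. The price is that the later places in a block follow from the earlier ones. That matters little when past allocations are hidden. Here they are very likely visible to investigators, who have to titrate by drug and apply a rule that depends on the arm. A central randomiser hides the list, but it does not stop deduction from allocations already revealed.

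Foreknowledge does harm only if enrolment leaves some choice. Some choice exists: whether a patient is stable at dry weight, whether a medical condition counts as unstable, and when a patient is put forward. The arms also have different calcium and phosphate limits, so a recruiter who knew the next drug could have a reason to delay or pass over a particular patient. At stake is the comparability of the arms on features other than baseline LVMI and the stratification factors, which are the covariates named for the primary model. Fluid status is one such feature, and the Background names volume overload among the main drivers of cardiac remodelling.

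**Working it through.** The article gives no figure for predictability, so there is none to reproduce.

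**Inputs.** Block size 4, ratio 1:1, two stratification factors with two levels each (4 strata), from the randomization section. 62 randomised patients, from the Abstract and Study design. Centre sizes of 160 and 300 prevalent patients, from Study design. Assumptions: blocks run within strata, and the observer knows the block size and every earlier allocation in the stratum.

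**One complete block.** Two places per arm give 6 equally likely orders.

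- Certain in advance: places 1 and 2 never are. Place 3 is certain if the first two match (2 of 6 orders = 1/3). Place 4 always is. Total 1/3 + 1 = 4/3 per block, and (4/3)/4 = 1/3 = 33%.
- Best guess (always the arm with more places left): place 1, 1/2; place 2, 2/3; place 3, 1/3 × 1 + 2/3 × 1/2 = 2/3; place 4, 1. Total 17/6, and (17/6)/4 = 17/24 = 71%, against 50% under simple randomisation.

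**62 patients with incomplete last blocks.** If a stratum's size is equally likely to leave a remainder of 0, 1, 2 or 3 after division by 4, the mean remainder is 1.5, and only a remainder of 3 adds a possible certain place (probability 1/3). Expected certain allocations in a stratum of n patients are therefore (n − 1.5)/3 + (1/4)(1/3) = n/3 − 5/12. Over four strata: 62/3 − 4 × 5/12 = 20.67 − 1.67 = 19.0, and 19.0/62 = 31%.

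A simulation of 1,500 runs agrees, and the result hardly depends on the level at which the blocks run:

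| Blocks of 4 run within | Certain, of 62 | Best guess correct |
|---|---|---|
| 4 equal strata | 19.0 (30.6%; 95% range 15 to 23) | 69.7% |
| 4 strata, centres 160:300, urine split 50:50 (assumed) | 19.0 (30.6%) | 69.7% |
| Centre only | 19.8 (31.9%) | 70.2% |
| One single list | 19.9 (32.1%) | 70.5% |

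**Randomly varying sizes** (4 equal strata, sizes equally likely; the observer knows the possible sizes but not the size of each block):

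| Sizes | Certain, of 62 | Best guess correct |
|---|---|---|
| 4 only (as planned) | 19.0 (31%) | 70% |
| 2 and 4 | 6.3 (10%) | 71% |
| 4 and 6 | 3.7 (6%) | 68% |
| 4, 6 and 8 | 1.5 (2%) | 67% |

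Varying the size removes most of the certainty and little of the average guessability.

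**Precision of a retrospective check.** With about 19 certain allocations, or 9 to 10 per arm, and the planning SD of 25 g/m², the standard error of a baseline LVMI difference is 25 × √(2/9.5) = 11.5 g/m². With t on 17 degrees of freedom (2.11), the 95% half-width is 2.11 × 11.5 = about 24 g/m², wider than the 20 g/m² target effect.

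**The case against.** The strongest reply is that the article contains no error here. A small fixed block serves its stated aim of balance with 62 patients over up to four strata. The article does not say who enrols patients, whether they also treat them, or whether anyone could tally allocations by stratum. Role separation and access to the randomiser commonly sit in the full protocol, so silence on them is no defect. Most eligibility criteria are measured: PTH, calcium, time on dialysis, septum thickness, bioimpedance and lung ultrasound. Baseline MRI precedes randomisation, the outcome readers are blinded, and the model adjusts for baseline LVMI and the strata.

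Much of this stands. Knowledge of past allocations and blocks within strata are inferences, though strong ones, and the 31% describes an observer with a perfect tally. The protections limit detection bias and imbalance in LVMI, but they do not prevent selection on other prognostic features. The constant block size is itself a stated choice, so it can be judged as it stands.

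Three stronger readings are tempting and unsupported:

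- A reader might infer that enrolment was in fact steered. Nothing in the article shows this.
- A reader might blame publication of the block size. The article appeared on 24 October 2019, about a month before enrolment was expected to end, so the exposure comes from staff knowing the size during recruitment.
- A reader might count the length of the washout among the recruiter's choices. It is fixed at 4 weeks wherever it is mentioned; only the timing of enrolment is open.

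**Conclusion.** The point holds as a minor, inexpensive improvement to the design. A constant block size of 4 makes about 31% of the 62 allocations certain for someone who knows the size and keeps count, and lets such a person guess about 70% correctly overall. This rests on three assumptions: investigators know the assigned drug, recruiting staff know the block size and earlier allocations, and blocks run within strata. The last hardly affects the figure (31% to 32% across the alternatives). The room for selection is limited to a few judgements of eligibility and timing. The documents support a risk only; they give no basis for computing a bias in the treatment effect or for saying that the result is compromised.

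**What to change.** For every patient still to be randomised, set the web randomiser to randomly varying block sizes, for example 4 and 6, within the existing strata, and withhold the sizes from recruiting staff. Sizes of 2 and 4 would be a poorer choice, since they leave 10% of allocations certain and do not reduce guessability.

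The cost is a setting in the tool and slightly larger possible imbalance: a block of 4 can leave a stratum at most 2 patients out of balance, a block of 6 at most 3. The primary ANCOVA already includes the stratification factors. The benefit is limited to the few patients not yet randomised, so the 6% describes the scheme had it been used throughout and cannot be reached now.

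For patients already randomised, report an exploratory comparison of baseline characteristics against the allocation probability predicted from the sequence within each stratum. Include variables beyond LVMI, such as fluid status, calcium and phosphate, because the model already adjusts for LVMI. State its low precision beside the result: a null finding would not exclude selection. It needs only the allocation log and baseline data.

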**Fig. 1 Fig1:**
[figure not shown]
Study flow chart. cMRI cardiac magnetic resonance, Echo echocardiography, FGF23 fibroblast growth factor 23, RAAS renin–angiotensin–aldosterone system

**Fig. 2 Fig2:**
[figure not shown]
Study design. BCM body composition monitoring, cMRI cardiac magnetic resonance imaging, Echo echocardiography, Vit vitamin

### Treatment phase

The treatment phase starts with a dose-titration phase of 16 weeks. Subjects will be considered for dose titration of the investigational product every 4 weeks. Dose adjustment will be based upon PTH values, serum electrolytes and safety assessment. Study visits will take place in 2-week intervals during the first 10 weeks of treatment followed by study visits every 4 weeks. The duration of the treatment phase is 12 months.

### Study endpoints

The primary endpoint is the change in LVMI (quantified in grams per meter squared) from baseline to 12 months between the ETL and ALFA groups as assessed by cMRI.

Secondary endpoints are the change in left atrial diameter (measured in millimeters), the change in LVMI and left atrial diameter progression (percent), the difference in cardiac fibrosis and fibrosis progression as measured with noncontrast T1 mapping (milliseconds) and differences in cardiac function (ejection fraction, measured as percent) as well as wall motion abnormalities (percent change) as measured by cMRI and strain echocardiography after 1-year treatment with either drug. Other secondary objectives include changes in serum levels of FGF23, s-Klotho, PTH, 25-hydroxyvitamin D (25(OH)D) and 1,25-dihydroxyvitamin D (1,25(OH)_2_D), phosphate, calcium, pro-brain natriuretic peptide (proBNP), pre- and postdialysis troponin T (TnT) and the metabolites of the RAAS cascade (Ang I, Ang II, Ang-(1–7), Ang-(1–5), Ang-(1–9), aldosterone) under either treatment as well as their association with the abovementioned cardiac changes.

### Outcome measurements

#### Cardiac MRI

Two cMRIs are planned for each patient. The baseline MRI will take place before randomization and the second MRI will take place after completing 12 months of treatment. Both will be carried on the dialysis-free day.

The cMRI will be analyzed by one radiologist blinded to the treatment allocation. Noncontrast cMRI will be carried out using a 1.5-Tesla MRI scanner (Siemens Avanto 1.5 T, Siemens, Erlangen, Germany). Axial black-blood imaging will be performed for visualization of cardiac anatomy. For the assessment of cardiac function, left ventricular muscle mass, and the visualization of possible wall motion abnormalities, multislice-multiphase cine imaging will be performed in the long horizontal axis as well as in the short axis view through the entire heart. The ejection fraction (in percent) of both the left and right ventricles will be calculated in a semiautomatic fashion using dedicated software (Siemens Argus) based on the short axis views. For the assessment of cardiac function, the end-diastolic and end-systolic volume (in milliliters) will be assessed in a semiautomatic fashion and the left ventricular muscle mass will be calculated [42]. The upper limit of normal left ventricular mass indexed for body surface area (LVM/BSA) values is considered to be 84.1 g/m^2^ for male and 76.4 g/m^2^ for female subjects [6].

For the detection of myocardial fibrosis, fat-suppressed T2-weighted edema-sensitive imaging will be performed. Noncontrast T1 mapping will be performed to detect diffuse fibrotic processes (T1 time is measured in milliseconds for global, septal and nonseptal times). The native myocardial T1 relaxation is a surrogate of myocardial fibrosis [43]. In hemodialysis patients the interventricular septum appears to be particularly prone to the development of fibrosis [44].

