### Safety evaluation and reporting of adverse events

The investigators ensure that adequate medical care is provided in any clinical situation, including emergencies. All AEs observed by the investigator or reported by subjects are to be properly captured in the subjects’ medical records. This collection period will be from the time of the first dose of the investigational product to 30 days after the last dose.

It will be left to the investigator’s clinical judgment to determine whether an AE is related and of sufficient severity to require the subject’s removal from treatment. As defined by the International Conference on Harmonization guidelines and World Health Organization Good Clinical Practice guidelines, serious AEs are events that result in patient death, are life-threatening, require or prolong hospital stay, cause persistent or significant disability or incapacity, result in congenital anomaly or birth defect, or necessitate specific interventions. Events that are suspected unexpected serious adverse reactions (SUSARs) will be reported to the responsible ethics committee — the European Medicines Agency via the Clinical Trials Coordination Center of the Medical University of Vienna. Fatal SUSARs will be reported as soon as possible, but at the latest within 7 days and nonfatal SUSARs within 15 days.

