### Statistical methods

Data will be described as means and standard deviation or medians and interquartile range for continuous symmetric and skewed variables, respectively. Distributions of the analyzed parameters will be visualized by boxplots and histograms.

The primary endpoint (change in LVMI from baseline to 12 months) will be analyzed by the analysis of covariance. The main variable in the model to be tested will be treatment group, which represents the treatment effect on change in LVMI 1 year after baseline between the two treatments. Baseline LVMI for each patient will be used as a covariate in the model and the interaction between treatment group and baseline LVMI will be included. Furthermore, to account for stratification during randomization, the stratification factors will also be included in the model. The secondary endpoints (changes in FGF23, s-Klotho, PTH, 25(OH)D, 1,25(OH)_2_D, proBNP, pre- and postdialysis TnT and RAAS metabolites) will be analyzed analogously. All analyses will be conducted according to the intention-to-treat principle. Two-sided *p* values lower than 0.05 will indicate statistical significance.

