### Sample size calculation

On the assumption, based on published data, that the mean LVM/BSA of hemodialysis patients determined by cMRI is 100 g/m^2^ with a standard deviation of 25 g/m^2^ [42] and an expected treatment effect of delta LVMI of 20 g/m^2^, 25 patients are needed per group to detect this difference with 80% power using a two-sample *t* test at an alpha level of 0.05. Assuming 10% attrition (drop out/loss to follow-up) within 1 year of follow-up, the final sample size in the intention-to-treat analysis will be 31 patients.

Patients receiving a renal transplant as well as those who become pregnant (which is unlikely due to the significantly reduced fertility of women under dialysis) will drop out of the study.

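### The only follow-up MRI is tied to completing treatment, while the primary endpoint is defined by time and the analysis by intention-to-treat; the scan should be set at month 12 whatever the treatment status

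*Protocol article*

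**What the plan says.** - **Scan schedule (Cardiac MRI):** "Two cMRIs are planned for each patient". The first is before randomisation, and "the second MRI will take place after completing 12 months of treatment". There is no MRI in between.
- **Primary endpoint (Study endpoints):** the change in LVMI "from baseline to 12 months between the ETL and ALFA groups as assessed by cMRI". This is defined by time, not by treatment completion.
- **Analysis (Statistical methods):** "The primary endpoint (change in LVMI from baseline to 12 months) will be analyzed by the analysis of covariance", and "All analyses will be conducted according to the intention-to-treat principle".
- **Stopping drug (Safety evaluation and reporting of adverse events):** the investigator judges whether an adverse event calls for "removal from treatment". The section does not say whether the patient is then followed to month 12.
- **Leaving the study (Sample size calculation):** two groups are named, "Patients receiving a renal transplant as well as those who become pregnant", and they "will drop out of the study". The same section assumes 10% attrition and puts 31 patients in the intention-to-treat analysis (read as per group, since 62 are randomised).

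**The concern.** A time-based endpoint analysed by intention-to-treat needs a month-12 LVMI from each randomised patient who can still be scanned. A scan that depends on finishing a year of treatment delivers it only for those who finish. The two rules agree for completers and part for anyone who stops drug but remains in the trial.

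This concerns data collection, not analysis. No analysis plan can recover a scan that was never taken, and with a single follow-up MRI there is no intermediate LVMI to stand in for it. If patients who stop drug differ in their LVMI course from those who continue, and do so differently by arm, the comparison of scanned patients no longer has the protection of randomisation.

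**Working it through.** **Step 1. The sections side by side.**

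| Patient | Month-12 LVMI needed under a time-based endpoint and intention-to-treat | Second MRI under the literal scan rule |
|---|---|---|
| Completes 12 months of drug | yes | yes |
| Taken off drug, stays in study | yes | no |
| Transplanted or pregnant | leaves the study as stated | no |

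The conflict is in the second row. Other sections use similar timing: the cMRI and strain echocardiography secondary endpoints refer to one year of treatment, and the final echocardiogram and RAAS fingerprint come at the end of the treatment phase. No section says that patients off drug are followed to month 12.

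**Step 2. The plan's own figure.** Inputs from Sample size calculation: difference 20 g/m², SD 25 g/m², power 80%, alpha 0.05 (two-sided).

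n per group = 2 × (1.96 + 0.84)² × (25/20)² = 24.5, rounded up to 25. This reproduces the stated 25. The exact t test gives 25.5, so 26; with 25 per group its power is 79.1%.

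**Step 3. How many might be unscanned.** The article gives no rate of stopping drug. As a stand-in, the attrition allowance gives a range:
- the stated 10% of 31 is 3.1, about 3 per group;
- the margin between 31 randomised and 25 needed is 6 per group (6/31 = 19%).

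With 3 unscanned, an ANCOVA on observed change uses about 28 per group, not 31.

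**Step 4. Possible shift in one arm.** If k of 31 are unscanned and their mean change differs by D from that of scanned patients, the mean of all 31 differs from the scanned mean by (k/31) × D.

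| k | D = 12.5 g/m² | D = 25 g/m² |
|---|---|---|
| 3 | 1.2 | 2.4 |
| 6 | 2.4 | 4.8 |

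Against 20 g/m² this is 6% (1.2/20) to 24% (4.8/20). D is an assumption. The 25 g/m² is the stated SD of LVMI level, not of 12-month change, and serves only as a yardstick. The table takes one arm alone; equal losses with equal D in both arms would cancel.

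**The case against.** The strongest reply is that the sentence is ordinary visit timing. It follows directly on the statement that two scans are planned for each patient, the treatment phase lasts 12 months, and the endpoint is defined at 12 months. On that reading everyone is scanned at month 12. This reply stands in part: the wording allows both readings, but nothing in the article settles which one a site should follow when a patient is off drug.

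Four stronger readings are tempting, and the document does not support them:

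- **That the primary analysis is a completers analysis.** No section restricts it so, and Statistical methods says the opposite. It becomes one only if the scan rule is applied as written.
- **That everyone who stops simply leaves.** Leaving the study is stated only for transplant and pregnancy. Adverse events lead to removal from treatment, not from the study.
- **That missingness is treatment-related.** The Investigational products section gives different calcium and phosphate limits by drug, but as limits on titration. It reports no stopping rates by arm, so the mechanism is plausible only.
- **That the absence of a missing-data rule is an error.** Imputation and the handling of transplanted or deceased patients are commonly left to the full protocol or analysis plan. Some missing outcomes under intention-to-treat are not in themselves a contradiction.

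**Conclusion.** The point holds in a limited form. A stated data-collection rule, read literally, withholds the primary outcome from patients who stop drug but stay in the trial, which does not fit the time-based endpoint or the intention-to-treat statement. The illustrated shift of about 1.2 to 4.8 g/m² in one arm's mean rests on assumed counts and an assumed difference between unscanned and scanned patients. It shows what could be at stake and is not an estimate of bias. This is a cheap improvement worth making, not a flaw that invalidates the plan.

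**What to change.** Reword the sentence in Cardiac MRI along these lines: *the second MRI takes place 12 months after randomisation in every randomised patient who is alive, still consenting and able to be scanned, whether or not study drug was stopped.* Then reconcile Study endpoints, Cardiac MRI, Statistical methods and Sample size calculation, including the count of 31 in the intention-to-treat analysis beside 10% attrition and the statement on patients who leave the study.

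**Cost.** One sentence, and a few already planned scans in patients off drug. Enrolment was expected to run to November 2019 and the article appeared on 24 October 2019, so anyone randomised in the preceding 12 months still had this scan ahead.

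**Downside.** The effect estimate may be somewhat diluted. If those who stop kept none of the 20 g/m² effect, all 31 per group were scanned and the SD stayed at 25 (all assumptions), 10% stopping gives 0.9 × 20 = 18 g/m² with 79.6% power, and 20% gives 0.8 × 20 = 16 g/m² with 69.8%. With the full 20 g/m² and 31 per group, power is 87.3%. That dilution belongs to the intention-to-treat question that the article says it asks.
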